## Abstract

**Background:**

Childhood obesity represents a global public health crisis: the number of obese children and adolescents (aged 519years) worldwide has risen tenfold in the past four decades. The vast majority of overweight and obese children live in high-income countries, and low socio-economic status (SES) is a significant risk factor. Family Based Interventions (FBI) have demonstrated positive results in preventing obesity, although these results are strongly influenced by SES. Moreover, we still poorly understand how FBI can determine a positive trend in weight status in low-income communities. Therefore, there is an urgent need to define and evaluate innovative and multi-target projects to reduce obesity risk behaviors and health inequalities and the present study aims to present the study protocol of FIVALIN a FBI that pretends to achieve this goal.

**Methods:**

We will conduct a quasi-experimental design within 60 Community Child Centers (CCC) in Barcelona metropolitan area. Each cluster (CCC) will be assigned by convenience to the intervention and control groups. For the whole study, a total of 810 children aged 812years and 600 parents will be recruited during 3 consecutive editions (1st 2019/2020; 2nd 2020/2021; 3rd 2021/2022) of 10months each. The action is a regular multicomponent health-promotion intervention targeting children, families, and CCC. All activities are based on the Motivational Interviewing (MI) approach and will focus on promoting good dietary habits, physical activity, appropriate screen time and sleep duration, and psychological well-being. The control group participate in a unique workshop on general awareness of healthy lifestyles for families. We will perform a comparative analysis of the evolution of weight status, healthy lifestyles, and socioeconomic variables, between the intervention and control groups.

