### Subjects

The study will involve low SES children aged 812years and their families from 60 Community Child Centers (CCC) in the metropolitan area of Barcelona. A CCC is a childcare center that promotes the education of children from low income families by providing them academic support and emotional education after school. A total of 810 children and 600 parents will be included in the intervention groups, and likewise for the control groups. These population samples will be distributed among three consecutive editions of the FIVALIN project (20192020, 20202021, and 20212022), and will include at least one adult and one child per low-income family. A total of 30 CCC (15 in the intervention group and 15 as controls) will be involved per edition. CCC from control group will be invited to be part of intervention group on the subsequent edition, and15 new CCC will be recruited in the control groups of the second and third editions. In total, after the three edition, 60 CCC will be enrolled in the project (see Table1). It is not expected that CCC participating in the intervention group during first or second edition will continue providing the intervention in subsequent editions. 18 socioeconomic vulnerable children (8- to 12-year-old) and their families will participate per CCC. Therefore, considering the intervention and control groups, we expect a total participation of 540 children and 400 adults per edition. Participants will be recruited by CCC, by inviting families that are already participating in their activities. They receive communicative material (flyers and leaflets) to introduce the project and motivate them to participate. For convenience, recruitment and allocation will be conducted by Gasol Foundation (GF), considering the characteristics of the CCC: activities, number of educators, parents involvement, etc.

**Table 1 Tab1:** Number of CCC per FIVALIN edition

CCC from the	1st edition	2nd edition	3rd edition
Intervention group	1 to 15 CCC *(new)*	CCC from the control group of the 1 edition 16 to 30 CCC	CCC from the control group of the 2 edition 31 to 45 CCC
Control group	16 to 30 CCC *(new)*	31 to 45 CCC *(new)*	46 to 60 CCC *(new)*

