### Sample size calculation

We estimate that it will be necessary to include 270 children and their parents, both in the intervention and control groups, per edition of the FIVALIN project. We expect a statistically significant decrease in body mass index (BMI) z-score of 0.15 in the intervention group, in comparison to the control group. From the PRE to POST evaluations, for each of the three editions. Previous community intervention [35] that aimed to prevent childhood obesity through the promotion of healthy lifestyles, and were carried out in the same geographical context and among children of the same ages. They showed a mean zBMI reduction of 0.10. The FIVALIN project is a more intense intervention and, for this reason, we expect a higher zBMI reduction.

We assume a 0.05 alpha risk, a 0.2 beta risk in a bilateral contrast, and 20% loss to follow-up. We expect to recruit significantly less families with 2 children in the age range of 8 to 12years, than families with one child. Therefore, we performed a simplified approximation of the sample size by counting only for one outcome (zBMI of one child). The sample size was calculated using the online sample size and power calculator GRANMO (IMIM-Spain).

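### The abstract's whole-study total of 810 children and 600 parents is half of what the Subjects section adds up to, and the adult count implies more siblings than the one-child sample size approximation allows for

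*Protocol article*

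**What the plan says.** The Abstract (Methods paragraph) gives a size for the study as a whole: "a total of 810 children aged 812years and 600 parents will be recruited during 3 consecutive editions" (the dash in the age range 8 to 12 has dropped out).

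The Subjects section attaches the same two numbers to each arm: "A total of 810 children and 600 parents will be included in the intervention groups, and likewise for the control groups". It also supplies the components:

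- Centres per edition: "A total of 30 CCC (15 in the intervention group and 15 as controls) will be involved per edition".
- Children per centre: "18 socioeconomic vulnerable children (8- to 12-year-old) and their families will participate per CCC".
- Both arms together, per edition: "we expect a total participation of 540 children and 400 adults per edition".
- Family composition: the sample "will include at least one adult and one child per low-income family".
- Centres overall: "In total, after the three edition, 60 CCC will be enrolled in the project". Control centres are invited to move to the intervention group of the following edition (Table 1).

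The Sample size calculation section asks for 270 children and their parents per arm and edition. Its inputs are a zBMI difference of 0.15, two-sided alpha 0.05, beta 0.2 and 20% loss. On siblings it says: "We expect to recruit significantly less families with 2 children in the age range of 8 to 12years, than families with one child". On that ground it counts the zBMI of one child only, and calls this a simplified approximation. It states no SD.

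**The concern.** The article states its own size twice, and the two statements differ by a factor of two. The abstract is the part most often read and extracted, so the wrong total is the one likely to be carried forward.

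The second issue concerns the premise of the sample size. Treating 270 children as 270 independent observations is reasonable if families with two participating children are rare. The recruitment figures in the Subjects section suggest they are not. Outcomes of siblings are likely to be correlated, so the information in 270 children is then less than the calculation assumes, and the stated 80% power for each edition is somewhat optimistic.

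**Working it through.** **Counts.** Inputs are from the Subjects section and Table 1.

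- Children per arm and edition: 15 × 18 = 270. This agrees with the sample size section.
- Children per edition, both arms: 30 × 18 = 540, as stated.
- Children per arm, three editions: 3 × 270 = 810, as stated for each arm.
- Children, both arms, three editions: 2 × 810 = 1,620.
- Adults per arm and edition: 400 / 2 = 200. Per arm over three editions: 600. Both arms: 3 × 400 = 1,200.

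The Methods figures therefore agree with one another, and 810 and 600 are per-arm totals.

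Could the abstract mean unique people? Suppose every family in the 30 centres that cross from control to intervention were the same and were counted once. The totals would be 60 × 18 = 1,080 children and 60 × (400 / 30) = 800 adults. That is not 810 and 600 either.

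**Siblings.** Each family brings at least one adult, so the number of families cannot exceed the number of adults. Per arm and edition:

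- Families: at most 200.
- Children beyond one per family: at least 270 − 200 = 70.
- With 200 families and no more than two children each: 70 families with two children and 130 with one. That is 70 / 200 = 35% of families and 140 / 270 = 52% of children.
- Any family with two participating adults lowers the number of families and raises these shares. With 180 families (20 of them bringing two adults), two-child families number 270 − 180 = 90, already as many as one-child families.
- If some families bring three children, fewer families hold the 70 extra children.

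**Effect on per-edition power.** No SD is given, so it is back-solved from the plan's own target.

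- Evaluable per arm: 270 × 0.8 = 216.
- SD = 0.15 × √(216 / 2) / (1.960 + 0.842) ≈ 0.556. By construction this reproduces 270 per arm and 80% power. It does not confirm that the authors used this SD.
- Design effect for 130 singletons and 70 pairs: 1 + (Σm² / Σm − 1) × ρ, with Σm² = 130 + 4 × 70 = 410 and Σm = 270. This gives 1 + 0.519ρ.
- Power is recomputed with 216 divided by the design effect, which assumes that losses leave the mix of family sizes unchanged.

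| Sibling correlation ρ (assumed) | Design effect | Effective n per arm | Power | Children per arm for 80% |
|---|---|---|---|---|
| 0 | 1.00 | 216 | 80% | 270 |
| 0.1 | 1.05 | 205 | 78% | 284 |
| 0.3 | 1.16 | 187 | 74% | 313 |
| 0.5 | 1.26 | 172 | 70% | 340 |

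These figures allow for siblings only. Clustering by centre is not included.

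**The case against.** The case on the other side is substantial, and part of it stands.

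- **The count conflict is a slip in the abstract.** The Methods are coherent, and no calculation or analysis uses 810 as a whole-study total. That is true. It makes the correction easy, but the abstract is still wrong as written.
- **Siblings are not overlooked.** The sample size section mentions two-child families, expects fewer of them than one-child families, and labels its method an approximation. A split of 70 to 130 fits the direction of that expectation. This stands: it is a disclosed simplification, not an omission. What remains is that about a third of families and half of children is too large a share to leave out without justification.
- **Size of the power loss.** The documents give no sibling correlation. The modelled outcome is adjusted for baseline zBMI, so the relevant correlation could be low, and at 0.1 the loss is about two percentage points.
- **The analysis itself.** The Statistics section pools the three editions and fits GEE models with the centre as cluster. This already covers siblings who attend the same centre, so the validity of the test is not at issue. With 3 × 216 = 648 evaluable per arm, the same SD and a design effect of 1.26, pooled power would be about 99%, ignoring centre clustering and repeat participation. However, the sample size section sets its 0.15 target for each edition, so the per-edition power is the figure it claims.

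A reader might go further and infer that the 270 must be families, that only 200 are planned, and that power should be computed on one child per family. The documents do not support this. The stated unit is children, and the GEE analysis is at individual level with no provision to discard siblings.

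A reader might also infer that 1,620 is a count of repeated records and not of unique children. The text says only that control centres are invited into the next intervention group. It does not say whether the same children return.

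**Conclusion.** The count conflict is certain and needs no assumption: the abstract gives 810 children and 600 parents for the whole study, and the Methods give 1,620 and 1,200 participations.

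The sibling point is secondary. The ceiling of 200 families for 270 children per arm and edition follows from the stated figures alone. The shares of 35% and 52% also assume 200 families and no more than two participating children in each. The power figures of 78% to 70% rest on a back-solved SD and on assumed correlations of 0.1 to 0.5. They show moderate planning optimism for a single edition, not a flaw in the planned analysis. Both points should be corrected, and neither calls for a change in design.

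**What to change.** 1. In the abstract, give 1,620 children and 1,200 parents for the whole study (810 and 600 per arm), in line with the Subjects section.
2. Say whether these totals are participations or unique people. Only the authors can supply this, because it depends on whether families in centres that cross over take part twice.
3. In the sample size section, state the expected number of families per arm and edition, and the SD used. Then either restate the per-edition power with a sibling allowance over a range of correlations, or reconcile the adult count if 200 adults per arm and edition was not meant to cover every family. The Discussion already refers to first-edition participants, so the actual number of families and sibling sets could be counted.

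The cost is a few lines of text and a per-edition power that may read slightly less favourably. The analysis model needs no change on this account.

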**Discussion:**

There is a need for more evidence on how to target and evaluate holistic interventions in low SES families. Our multi-targeting intervention for obesity prevention tackles risky behaviors that go beyond diet and physical activity (PA). Therefore, future interventions can effectively promote all the behavioral domains that determine trends in the weight status.

**Trial registration:**

ISRCTN Registry: ISRCRN12682870. Registered 9 July 2020. Retrospectively registered.

Protocol version: 30 April 2021, version 5.

**Supplementary Information:**

The online version contains supplementary material available at 10.1186/s12887-021-02697-x.

## Background

Pediatric obesity is considered one of the most serious public health issues of the twenty-first century [1]. In Spain, there is a special concern due to the high prevalence of overweight and obesity affecting the 34.9% of children aged 816years [2]. This prevalence is one of the highest rates in Europe [3]. Overweight and obesity have several consequences, as almost every organ system can be severely damaged, leading to cardiovascular and musculoskeletal diseases, metabolic complications, gastrointestinal disorders, and pulmonary dysfunction [4]. In addition, in children and adolescents, these health conditions are related to psychosocial disorders, such as depression, anxiety, and low self-esteem [5, 6]. These disorders are caused by an interaction between individual and contextual factors [7]. There is a well-studied association between obesity and some personal determinants, such as dietary habits [8], physical activity (PA) [9], sleep [10, 11], and psychological well-being [12, 13]. Similarly, environmental variables, such as parental and socioeconomic characteristics, likely contribute to the problem [13,15]. Indeed, higher levels of childhood obesity have been consistently found in children with a low socio-economic status (SES), leading to health inequalities [16].

Inequalities in childhood obesity seem to have increased in developed countries during the last two decades [16, 17]. These imbalances are related to economic development, cultural factors, and social and health policies [18, 19]. In high-income countries, low SES is associated with 16% higher risk of overweight, and 43% higher risk of obesity in children aged 015years [20]. In Spain, the percentage of 2- to 17-year-old children with obesity is 11.45% higher in families where mothers have a lower SES [21]. In particular, in Catalonia, 0- to 14-year-old children of mothers with a low level of education have a 5.33% higher level of obesity, in comparison to children of highly educated mothers [22]. A recent study in Catalonia between 2006 and 2016 showed that this health condition tends to increase or be maintained in children from deprived areas, whereas richer regions showed a downward trend [23]. In particular, in Barcelona city, different factors play an important role on childhood obesity prevalence: social class, geographical origin, family status, and the district of residence [24].

The reasons why children from low SES are at higher risk of becoming overweight are likely to be multifaceted and determined by different parameters: i) structural factors, such as food advertising and marketing [25]; ii) community factors, like neighborhood [26] (demonstrated in the Spanish context) [27]; and iii) individual lifestyles factors, such as daily PA [28]. However, family environment also plays an important role in the development of obesity in children [14]. Family Based Interventions (FBI) demonstrated positive results in preventing childhood obesity, but SES contributes to the complexity of reaching positive results [14, 29]. More evidence is needed to better understand parents influence on school age childrens lifestyles from disadvantaged backgrounds, which evidence suggest a strong relationship from early childhood [30]. Moreover, only a limited number of FBIs-targeted risk behaviors other than diet and PA [31, 32]. The successful FBI that pretend to produce a positive effect on weight status and lifestyles should follow a multicomponent and multilevel approach [33,35]. This means that educational family interventions should also tackle political and social factors. Moreover, they should involve the key sectors where families spend their daily time such as school, primary care centers, sport organizations, leisure time facilities, etc. in order to build full community-based interventions.

The FIVALIN study protocol will use a multiple behavioral approach to simultaneously target diverse risk behaviors, such as healthy eating, PA, screen time, sleep quality and duration, and psychological wellbeing. In this way, our study will give a more comprehensive view of the value of FBIs in preventing childhood obesity among low SES families.

## Methods

### Study design

To determine the effects of the FIVALIN project, we will perform a quasi-experimental design with a control group.

### Aim

The aim of this manuscript is to describe the study protocol of the FIVALIN (Acronym of FItness, VAlues and Healthy LIfestyles) project. This is an FBI to prevent pediatric obesity in 8- to 12-year-old children, through promoting healthy lifestyles, among low-income families in Barcelona.

### Subjects

The study will involve low SES children aged 812years and their families from 60 Community Child Centers (CCC) in the metropolitan area of Barcelona. A CCC is a childcare center that promotes the education of children from low income families by providing them academic support and emotional education after school. A total of 810 children and 600 parents will be included in the intervention groups, and likewise for the control groups. These population samples will be distributed among three consecutive editions of the FIVALIN project (20192020, 20202021, and 20212022), and will include at least one adult and one child per low-income family. A total of 30 CCC (15 in the intervention group and 15 as controls) will be involved per edition. CCC from control group will be invited to be part of intervention group on the subsequent edition, and15 new CCC will be recruited in the control groups of the second and third editions. In total, after the three edition, 60 CCC will be enrolled in the project (see Table1). It is not expected that CCC participating in the intervention group during first or second edition will continue providing the intervention in subsequent editions. 18 socioeconomic vulnerable children (8- to 12-year-old) and their families will participate per CCC. Therefore, considering the intervention and control groups, we expect a total participation of 540 children and 400 adults per edition. Participants will be recruited by CCC, by inviting families that are already participating in their activities. They receive communicative material (flyers and leaflets) to introduce the project and motivate them to participate. For convenience, recruitment and allocation will be conducted by Gasol Foundation (GF), considering the characteristics of the CCC: activities, number of educators, parents involvement, etc.

**Table 1 Tab1:** Number of CCC per FIVALIN edition

CCC from the	1st edition	2nd edition	3rd edition
Intervention group	1 to 15 CCC *(new)*	CCC from the control group of the 1 edition 16 to 30 CCC	CCC from the control group of the 2 edition 31 to 45 CCC
Control group	16 to 30 CCC *(new)*	31 to 45 CCC *(new)*	46 to 60 CCC *(new)*

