### Intervention

The FIVALIN project is an FBI addressed to school age children (8- to 12-year-old) and their parents/caregivers. It has been created to be part of a Multi-Level Multi Component (MLMC) intervention that pretends to prevent childhood obesity from early ages, and along all the developmental stages, until adulthood. The pre-adolescence stage is a key period to sustain the healthy lifestyles promotion activities to prevent a deterioration at subsequent stages.

The FIVALIN project will be developed in three editions (1st 2019/2020; 2nd 2020/2021; 3rd - 2021/2022) of 10months each. The plan will be coordinated by the multidisciplinary health team of the GF, supported by educators of the CCC and a trained team of volunteers. We expect that the GF team will be stable. To ensure intervention consistency, we will activate different strategies (see Additionalfile1). Volunteers will be recruited by GF. They will contact the entity and, after a welcoming training, they will be involved in the project activities.

The study will be conducted after school time in CCC in the metropolitan area of Barcelona. In CCC, parents are encouraged to be part of their childrens education. For the intervention group, we define two modalities of participation (low and high), depending on the project intensity. The main difference between the two modalities is that children participating in the high intensity modality will do an extra activity, attending 32 sports educational sessions implemented by CCC educators. Each CCC will choose the modality that best fits their internal organization (see Table2 and Figs.1, 2 and 3)*.* Additionally, educational material, mobile messages, and videos will be sent to families in order to reinforce the health behaviors promoted during the workshops and sport educational sessions. Moreover, mobile messages will remind workshops date and hour to promote the participants attendance. CCC participating in the control group will be invited to be part of the intervention group in the next edition. The control group will receive the usual care provided in the CCC program plus a pre-evaluation and post-evaluation session. Moreover, they will receive a family workshop aimed to generate healthy lifestyle awareness and engagement, in order to reduce shortcomings in the post-evaluation.

**Table 2 Tab2:** FIVALIN project activities description by participation options

Activity description	Intervention		Control
	High intensity	Low Intensity	

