### Statistics

We will analyze the pooled data from the three timely different editions with a 10-month intervention each. Data clean-up will be performed to minimize errors. To compare groups, we will use the Student-t test for continuous variables and chi-square test for categorical variables. Allocation to the intervention group will be performed at the CCC level (clusters) by convenience. Therefore, generalized estimating equation (GEE) models will be fitted to assess intervention effect on BMI z-score and other secondary outcomes at individual level. To assess the outcome at family level, we will apply mixed models.

Due to the small number of clusters, GEE models estimation will be followed by t test with the Kauermann and Carrol-corrected sandwich estimator. In alternative, we will use the Wald t test with the FG-corrected sandwich estimator, depending on the variation in cluster size (function saws from R package saws) [50]. FG-corrected sandwich estimation is not possible with mixed models. For this reason, we will apply GEE models for the analyses. BMI z-score and other secondary outcomes at baseline will be used as covariates to adjust the models. Final models will be adjusted for baseline covariates such as: age, sex, mothers educational level, adherence to the Mediterranean diet, PA, and the corresponding anthropometric variable (function mgee from R-packagesaws). A fidelity score will also be included as a covariate in the models. Differences between the intervention and control group were considered significant if *p*<0.05. All analyses will be carried out using SPSS V21.0 and R.

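### In editions 2 and 3 every planned intervention centre is a former control centre and every control centre is new, so arm and prior centre participation coincide in the pooled analysis; separately, the Abstract gives half the sample that Subjects gives

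*Protocol article*

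**What the plan says.** **Rollover.** Subjects sets the size of each edition: "A total of 30 CCC (15 in the intervention group and 15 as controls) will be involved per edition". It then provides that "CCC from control group will be invited to be part of intervention group on the subsequent edition", and the Intervention section repeats this: "CCC participating in the control group will be invited to be part of the intervention group in the next edition". Table 1 fills in the plan. The edition-2 intervention cell reads "CCC from the control group of the 1 edition 16 to 30 CCC", edition 3 uses centres 31 to 45 in the same way, and the control row is marked as new in all three editions.

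**What a control centre receives.** According to Intervention and Table 2, it gets a baseline and a final evaluation, one family workshop on healthy-lifestyle awareness, and educational material.

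**Who may enrol.** Families are recruited from those already attending the centre, and children are aged 8 to 12. The single exclusion criterion concerns inability to follow the assessments and activities; it does not exclude earlier participants.

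**Analysis.** Statistics says "We will analyze the pooled data from the three timely different editions with a 10-month intervention each". The model is a GEE, chosen because allocation is by centre. The covariates named are the baseline outcome, age, sex, mother's education, diet, physical activity and a fidelity score.

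**Totals.** The Abstract says "For the whole study, a total of 810 children aged 812years and 600 parents will be recruited during 3 consecutive editions" (ages 8 to 12). Subjects says "A total of 810 children and 600 parents will be included in the intervention groups, and likewise for the control groups".

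**The concern.** The pooled contrast is meant to compare intervention with control. In editions 2 and 3 it also compares centres in their second year of contact with centres in their first. Second-year centres and their families have been measured before, have had material that resembles a light version of the intervention, and have chosen to stay. Any effect of these on the 10-month change in BMI z-score is credited to the intervention.

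The Evaluation plan justifies pooling by keeping methods, activities and tools the same across editions. Prior contact in the intervention arm is not the same: it is absent in edition 1 and universal in editions 2 and 3 as planned. The Discussion reports similar groups only for the first edition, the one edition without this problem.

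If children return, the number of distinct children is smaller than the number of records. The conflicting totals are a separate matter, but they leave the reader unsure of the planned sample size.

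**Working it through.** **1. Reproduce the plan's counts.** Inputs from Subjects: 15 centres per arm per edition, 18 children per centre ("18 socioeconomic vulnerable children (8- to 12-year-old) and their families will participate per CCC"), three editions, 400 adults per edition.
- Children per arm per edition: 15 × 18 = 270, which agrees with Sample size calculation.
- Children per edition: 2 × 270 = 540, as stated.
- Children per arm over three editions: 3 × 270 = 810, as stated. Both arms: 1,620 child-edition records.
- Parents: 3 × 400 = 1,200 records, or 600 per arm, as stated.
- Distinct centres: 30 + 15 + 15 = 60, as stated.

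Subjects is therefore internally consistent. The Abstract's 810 and 600 are exactly one arm's worth, half of 1,620 and 1,200.

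**2. Count prior participation from Table 1** (assuming all invited centres accept).

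| Edition | Intervention centres with a prior control year | Control centres with prior participation |
|---|---|---|
| 1 | 0 of 15 | 0 of 15 |
| 2 | 15 of 15 | 0 of 15 |
| 3 | 15 of 15 | 0 of 15 |
| Pooled | 30 of 45 (67%) | 0 of 45 |

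The 90 centre-editions come from 60 centres. Thirty of these (16 to 45) appear once in each arm.

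**3. What a covariate could do.** A centre-level indicator of prior participation equals arm in editions 2 and 3 and is zero throughout edition 1. Within editions 2 and 3 it cannot be told apart from arm. Added to the pooled model with edition terms, it would leave the arm effect to be estimated from edition 1. An edition term alone removes differences between years, not this overlap.

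**4. Returning children.** Let r be the share of control children in the 30 rollover centres who re-enrol (not given; assumed). Repeat children = 30 × 18 × r = 540r; distinct children = 1,620 − 540r.

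| Assumed r | Repeat children | Distinct children |
|---|---|---|
| 0% | 0 | 1,620 |
| 25% | 135 | 1,485 |
| 50% | 270 | 1,350 |
| 80% | 432 | 1,188 |
| 100% | 540 | 1,080 |

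The last row is a ceiling. It needs every control child to be still within the age range and to return.

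**5. Sensitivity of the effect estimate.** Suppose a prior control year changes the later 10-month BMI z-score change by b (assumed; size and direction unknown). With equal weights the pooled effect shifts by (30/45) × b = 2b/3. Against the planned difference of 0.15:
- b = 0.02: shift 0.013, or 9%.
- b = 0.05: shift 0.033, or 22%.
- b = 0.10: shift 0.067, or 44%.

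**6. Sensitivity of the variance.** With m repeat children and within-child correlation ρ of the two changes (assumed), and leaving other centre clustering aside, the variance of the arm difference is (2σ²/810) × (1 − (m/810) × ρ). At m = 540 the factor is 1 − 0.667 × 0.6 = 0.60 for ρ = 0.6, and 1 + 0.667 × 0.3 = 1.20 for ρ = −0.3. Treating the records as independent could err in either direction.

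**The case against.** - **Only centres are invited onward.** The documents nowhere say that families or children re-enrol. This stands. A reader might infer that children are counted in both arms; the documents show only that nothing prevents it. Likewise 1,080 is the result of an assumed full return, not a third stated total, and the Abstract's 810 is no evidence about repeat children.
- **An analysis plan may cover it, and the covariate list is open-ended.** This stands as far as it goes: the lack of an edition term or a repeat-child rule in an article would not by itself be a finding. But the rollover and the pooling are fixed here, and an edition term would not separate arm from prior participation.
- **The GEE is clustered on the centre.** With one identifier per centre kept across editions, the sandwich variance would cover the correlation between a returning child's two records at that centre. So it cannot be said that the plan ignores that correlation; the article simply does not say whether there are 60 clusters or 90. This concerns standard errors, not the confounding.
- **The prior exposure is small and baseline is adjusted for.** The control year holds two evaluation sessions, one workshop and some material, and new controls receive the same during their own year. Baseline adjustment deals with a shifted starting level. What remains is an effect of earlier contact, or of selective staying, on later change. No size or direction is known, so no claim that the pooled result is biased by a given amount is supported.
- **Rollover is voluntary.** The exact overlap depends on full acceptance, which is what Table 1 plans.

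**Conclusion.** The point holds as a design limitation that the pooled analysis does not visibly address. Under Table 1 with full acceptance, 67% of intervention centre-editions and none of the control centre-editions have prior participation, and within editions 2 and 3 the two cannot be separated by modelling. Only edition 1 is free of the rollover. The limitations in the Discussion cover self-selection and non-random assignment but not this.

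Overlap of children between arms is possible, with a ceiling of 540 of 810 intervention children; its actual extent cannot be derived from the article. The shifts of 9% to 44% of the planned effect illustrate assumed values of b and are not estimates.

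The contradiction between the Abstract and Subjects is certain, a factor of two for both children and parents, and independent of the rest.

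**What to change.** 1. In the pooled GEE, cluster on the centre with one identifier kept across editions (60 clusters, not 90), and keep one identifier per child.
2. Include edition and arm-by-edition. A difference between edition 1 and the later editions would mix prior participation with ordinary differences between years, so it should be read with care.
3. Prespecify the edition-1-only estimate as the key sensitivity analysis and report it beside the pooled result.
4. Add a secondary sensitivity analysis that drops the repeat records of returning children, noting that it does not remove prior exposure at centre level.
5. State the rollover as a limitation.
6. Correct the Abstract to 810 children and 600 parents per arm, and report the number of distinct children.

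The cost is some analysis wording and a persistent identifier, with no new outcome measurements. The edition-1 estimate is less precise: after the planned 20% loss it rests on 270 × 0.8 = 216 children per arm instead of 810 × 0.8 = 648, so with independent records its standard error is about √3 = 1.73 times as large. The Sample size calculation does, however, set 270 per arm for each edition, so by the plan's own reasoning that comparison is one it means to support.
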